### Recruitment

The entire recruitment will be conducted on the web nationally through the National Center on Health, Physical Activity and Disability website and its associated social media. Through these mechanisms, interested individuals will be directed to a landing website page that will have promotional media content and information about the study. From there, participants will be directed to a separate link through HIPAA-compliant REDCap and complete a screening eligibility form. If deemed eligible, the participants will be sent an electronic consent form to be completed using the HIPAA-compliant REDCap. On the basis of our recruitment methods, we expect that approximately 180 individuals will be screened for eligibility.

### Allocation

Participants will be randomized to the two study arms in a 1:1 allocation ratio using a computer-generated randomization procedure. The allocation sequence will be implemented after the baseline surveys, and the baseline HbA_1c_ kit has been completed by the participant. The computer-generated randomization process will be implemented in REDCap after the data from the baseline surveys and HbA_1c_ kit are entered into the REDCap database. This will trigger the allocation procedure to randomly assign participants to one of the two study arms. The health coach will be notified about the randomization through the telecoaching dashboard and will inform the participants about their randomization into the AI4DM intervention or the attention control arm during the orientation call.

### Blinding (Masking)

The principal investigator and primary statistician will be blinded to the randomization of the participants into the study arms. All other study staff will be unblinded for purposes of recruitment, consent, orientation calls, welcome calls, coaching calls, and intervention package shipping. There are no circumstances in which the principal investigator or statistician will become unblinded during this protocol.

### Data Management

All data collected will be entered directly into REDCap. Participants will be assigned a subject number upon enrollment in the study. Only approved study personnel will have access to the REDCap program, where data will be stored. Data checking will involve confirming that surveys, questionnaires, and HbA_1c_ values are completed.

### Statistical Methods

All data will be examined for normality violations, outliers, errors, and patterns of missing values. For primary and secondary outcome measures, the sample and variables will be described using frequency distributions and appropriate summary statistics. Randomization across the study arms will be checked. If any baseline variable differs by group, it will be included as a covariate in subsequent analyses. Our primary analysis for the hypothesis that adults in the AI4DM intervention group will result in better glycemic control than the attention control group will be tested using analysis of covariance with baseline measurement as a covariate. Multiple imputations will be used to impute missing data. The study data will also explore the pattern and missing mechanism, and additional sensitivity analyses will be performed to test parametric assumptions as well as assumptions of missingness. Outliers and normality of quantitative variables will be evaluated. This study is powered to enable the estimation of effect sizes. Analysis of the clinical outcome (HbA_1c_) will control for the impact of medication and dosage during the intervention period.

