### Sample Size

A total of 90 participants will be enrolled. The sample size for this protocol is based on a primary analytic strategy of analysis of covariance, a two-sided test, type 1 error rate of 0.05, and intention-to-treat analysis with multiple imputations. Assuming a correlation between baseline and follow-up outcomes of at least 0.7, we will have 80% power to detect an effect size of 0.65.

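### Covariates for the primary HbA1c model are chosen by chance baseline imbalance, so the model is not fixed in advance; the direct cost is small, and the cure is a fixed covariate set

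*Protocol article*

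**What the plan says.** All the relevant text is in the protocol article, mostly under Statistical Methods. The arms are to be compared at baseline ("Randomization across the study arms will be checked"), and the result decides the covariates: "If any baseline variable differs by group, it will be included as a covariate in subsequent analyses". The sentence that follows describes the primary HbA1c comparison as "tested using analysis of covariance with baseline measurement as a covariate". The primary analysis is thus one of the analyses that the rule governs.

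One other adjustment is named: "Analysis of the clinical outcome (HbA_1c_) will control for the impact of medication and dosage during the intervention period". It concerns medication after randomization, so it is not a baseline prognostic covariate.

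Under Sample Size: "A total of 90 participants will be enrolled". The calculation assumes "analysis of covariance, a two-sided test, type 1 error rate of 0.05". It continues: "Assuming a correlation between baseline and follow-up outcomes of at least 0.7", "we will have 80% power to detect an effect size of 0.65".

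**The concern.** In a correctly randomized trial, any baseline difference between arms has arisen by chance. A comparison of arms at baseline therefore says nothing about which variables predict HbA1c. A rule that acts on it takes in variables that happen to differ, prognostic or not, and leaves out prognostic ones that happen to be balanced.

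Two things are at stake. First, the primary model is not fixed: which covariates it holds is known only once baseline data have been compared by arm. Second, precision that further prognostic covariates could give is mostly not obtained, because any one such variable enters only when it happens to be imbalanced.

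The point is the rule that the article states. It is not that the article leaves out a threshold or a list of variables, which a fuller document may give.

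**Working it through.** **Inputs from the protocol article.** 90 participants allocated 1:1, so 45 per arm; two-sided alpha 0.05; baseline to follow-up correlation 0.7; effect size 0.65 (Sample Size, Allocation). Table 2 lists eight questionnaire scales measured at baseline besides HbA1c, plus medication and dosage; Study Survey Packets adds a demographic survey of unstated length.

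**Assumptions.** Differing means p<0.05; 8 to 20 independent candidate variables; prognostic strength as shown below.

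**The plan's own power figure.** With outcome SD 1, the standard error (SE) from analysis of covariance is √(1−0.7²) × √(2/45) = 0.714 × 0.211 = 0.151. At 0.65 SD, 0.65/0.151 − 1.96 = 2.34, which is power of about 99%. The stated 80% is not reproduced. It appears if the correlation earns no credit and about 15% are lost: 38 per arm gives 81%, and 76/0.85 = 89.4, rounded up to 90. That loss is not stated. This is a separate matter and does not bear on the covariate rule. It does show that the effect detectable with 80% power is about 0.43 SD (0.427 from the t distribution), which is where power differences are visible.

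**How often the rule acts.** P(at least one flagged) = 1 − 0.95^k:

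| k | 8 | 10 | 15 | 20 |
|---|---|---|---|---|
| P | 34% | 40% | 54% | 64% |

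The expected number flagged is 0.05k, for example 0.75 at k = 15. Any one prognostic variable is picked up only about 5% of the time.

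**Type I error.** Simulation with no treatment effect, 45 per arm, correlation 0.7, 10,000 runs per row. One candidate explains the stated share of the residual variance.

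| Candidates | Share | Baseline HbA1c only | Imbalance rule | Covariate pre-specified |
|---|---|---|---|---|
| 8 | 10% | 0.0525 | 0.0495 | 0.0533 |
| 8 | 20% | 0.0451 | 0.0409 | 0.0463 |
| 8 | 40% | 0.0486 | 0.0369 | 0.0488 |
| 15 | 10% | 0.0523 | 0.0491 | 0.0523 |
| 15 | 20% | 0.0491 | 0.0468 | 0.0496 |
| 15 | 40% | 0.0505 | 0.0394 | 0.0522 |

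The simulation error is √(0.05 × 0.95/10,000) = 0.002. The rule does not inflate the error rate; it becomes conservative when a candidate is strongly prognostic.

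**Power and mean SE.** True effect 0.43 SD, 10 candidates, 10,000 runs per row.

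| Share | Baseline HbA1c only | Imbalance rule | Covariate pre-specified |
|---|---|---|---|
| 0% | 80.3%, 0.1511 | 79.0%, 0.1536 | 79.9%, 0.1520 |
| 10% | 80.1%, 0.1512 | 79.3%, 0.1533 | 83.0%, 0.1443 |
| 20% | 79.9%, 0.1512 | 79.6%, 0.1528 | 87.9%, 0.1359 |
| 40% | 80.4%, 0.1510 | 81.1%, 0.1517 | 94.8%, 0.1176 |

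The direct cost of the rule is the second column against the first. With no prognostic candidate the SE ratio is 0.1536/0.1511 = 1.017. With 15 candidates, one of them explaining 10%, it is 0.1543/0.1511 = 1.021.

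Two other set-ups at 0.427 SD agree. With three prognostic covariates explaining 10/20/30% in total (12,000 runs per setting), power is 83/86/91% if they are pre-specified and 78/79/80% under the rule. A further simulation with 15 candidates gives 82/86/90% against 77-79%.

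**At the stated effect of 0.65 SD.** Using mean SEs from the three-covariate set-up at 30%: under the rule, 0.65/0.153 − 1.96 = 2.29, power about 99%; with pre-specified covariates, 0.65/0.129 − 1.96 = 3.08, power above 99%.

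**The case against.** The strongest reply is that the sentence does little damage. Set against the baseline-only model, the rule costs about 1-2% in SE and about one point of power when nothing else is prognostic. The larger gap in power comes from adding good covariates, which is a separate design choice, and their strength is assumed; the document gives no figure for it. At 0.65 SD the gap almost vanishes. All of this stands.

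The plan also already pre-specifies the covariate likely to matter most. A reader might infer that it forgoes covariate adjustment altogether. It does not: at correlation 0.7, baseline HbA1c removes 0.7² = 49% of outcome variance.

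The article names neither a test nor a threshold, so the 34% to 64% range is conditional. Several scales are diabetes-related self-reports and are unlikely to be independent, and the upper figures depend on how many demographic items are counted. That too stands.

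Finally, the rule looks at baseline data and not at outcomes, is worded as mandatory, and the primary statistician is to be blinded to allocation (Blinding). A reader might infer that the model can be steered by results; the document does not support that. These safeguards limit discretion, but they do not fix the model in advance or make imbalance a sound guide to prognosis.

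**Conclusion.** The concern holds in a limited form. The article adopts a rule that lets chance imbalance decide covariates, and the rule reaches the primary HbA1c analysis. With 8 to 20 independent variables and a 5% threshold (both assumed), the fitted model would depart from the planned baseline-adjusted one in about 34% to 64% of correctly randomized trials.

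The size is modest: an SE about 1-2% larger, and type I error of about 0.04 to 0.05. A reader might infer a false-positive risk; the simulations show none for a mechanical rule. What is forgone is further precision beyond baseline HbA1c. At a true effect of 0.43 SD that is worth about 82-91% power against 77-80%, if other covariates explain 10-30% of residual variance (assumed). At 0.65 SD power is about 99% or more either way.

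The severity is moderate: this is a pilot of feasibility and preliminary efficacy, and nothing here invalidates it. The case for change is that a fixed model is better and costs only wording.

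**What to change.** - Remove the imbalance rule from the primary model.
- Fix that model in advance as arm, baseline HbA1c and, optionally, one to three named baseline prognostic variables, for example age or baseline medication. First confirm that each is collected: the article does not list the contents of the demographic survey. Disability type appears as an eligibility criterion, is not listed in the packet, and would use several degrees of freedom.
- Report baseline characteristics by arm descriptively, without tests.
- Allow models adjusted for observed imbalance only as labelled sensitivity analyses.

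The change needs no alteration to sample size or visits, and no new data if the chosen variables are already collected. The downside is a few degrees of freedom. One covariate that proves not to be prognostic raises the SE by 0.1520/0.1511 = 1.006, so three raise it by about 1.006³ = 1.018, or roughly 2%.

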### Study Survey Packets

After enrolling in the study, participants will automatically be emailed a Health Insurance Portability and Accountability Act (HIPAA)–compliant Research Electronic Data Capture (REDCap) link to a survey packet. REDCap is a secure program developed by a collaboration between Vanderbilt University and the National Institutes of Health National Center for Research Resources that manages and stores clinical trial data. This survey packet included a demographic survey and the secondary outcome measures listed in Table 2. Participants will be asked to complete this survey packet 4 times during the 12-month study period (excluding the demographics in the first survey packet). The timepoints included baseline, 3 months, 6 months, and postintervention (12 months).

**Table 2 table2:** Measures of efficacy.

Variables	Instruments	Time points
Glycemic management	HbA_1c_^a^ (clinical and primary outcome)	B,^b^ 3,^c^ 6,^d^ P^e^
Psychological distress	Diabetes Distress Scale	B, 3, 6, P
Quality of life	Diabetes Quality of Life Measure	B, 3, 6, P
Self-efficacy	Diabetes Empowerment Scale	B, 3, 6, P
Family support	Diabetes Family Behavior Scale	B, 3, 6, P
Physical activity	Godin leisure-time exercise questionnaire	B, 3, 6, P
Dietary intake	The UK Diabetes and Diet Questionnaire	B, 3, 6, P
Medication adherence	Medication Adherence Rating Scale	B, 3, 6, P
Telehealth dashboard usability	System Usability Scale & Health Information Technology Usability Evaluation Scale	3, 6, P
Health information technology	The eHealth Literacy Scale	B, 3, 6, P
Medication and dosage	Instruments for controlling medication and dosage during the analysis of the clinical outcome	B, 3, 6, P

^a^HbA_1c_: glycated hemoglobin.

^b^B: baseline.

^c^3: 3-month follow-up.

^d^6: 6-month follow-up.

^e^P: 12-month post–follow-up.

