### AI4DM Intervention Group Coaching Calls (First 12 Weeks)

Coaching calls for the intervention group will be guided by a prepared outline of diabetes-related content that will be delivered to the participant through the mHealth app. This content will be delivered at the beginning of each week before the coaching call. The educational content is derived from using the Partnership to Improve Diabetes Education program and delivered to the participant as multimedia content [36]. Other health-related areas covered during the coaching call will include nutrition and eating habits, exercise and PA, glucose monitoring, and medication adherence. Questions outside the scope of the health coaching content will be provided to the study clinician or registered dietician. If the study team determines that the questions require collecting a participant’s detailed medical profile, the participant will be guided to communicate with their primary care physician. Finally, the health coach will address other health-related questions that the participant may have. For each call, the health coach will be able to record notes in the telehealth app regarding topics discussed with the participant for future calls, as needed. Coaching calls are expected to last for up to 60 minutes.

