#### Medication and Dosage

Participants will be asked to provide current medications and dosages throughout the study duration to control medication data during the statistical analysis.

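### The HbA1c analysis is to control, without restriction, for medication and dosage recorded after randomisation, so it may not estimate the total effect of assignment and leaves the primary model unclear

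*Protocol article*

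**What the plan says.** Three places in the protocol article give medication data the same role.

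- **Statistical Methods:** "Analysis of the clinical outcome (HbA_1c_) will control for the impact of medication and dosage during the intervention period".
- **Table 2 (Study Survey Packets):** the medication row, with time points baseline, 3, 6 and 12 months, is described as "Instruments for controlling medication and dosage during the analysis of the clinical outcome". The same table labels HbA1c "clinical and primary outcome".
- **Medication and Dosage:** "Participants will be asked to provide current medications and dosages throughout the study duration to control medication data during the statistical analysis".

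None of the three limits the adjustment to baseline medication or to a sensitivity analysis.

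Earlier in Statistical Methods, the primary hypothesis on glycaemic control "will be tested using analysis of covariance with baseline measurement as a covariate". Medication is not mentioned there. The Sample Size section rests on "a two-sided test, type 1 error rate of 0.05, and intention-to-treat analysis with multiple imputations".

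The Randomization section places allocation after the baseline surveys and baseline HbA1c kit. Medication use in the intervention period therefore falls after allocation.

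**The concern.** A covariate measured after randomisation is safe in a treatment comparison only if the arm cannot affect it. Here the arm may do so:

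- AI4DM coaching covers glucose monitoring, and the technology package includes a wireless glucometer.
- For some questions outside the coaching scope, "the participant will be guided to communicate with their primary care physician".
- Under Attention Control Group Coaching Call, controls receive no diabetes-specific content.
- Everyone enters with HbA1c of at least 8% and not on insulin, which leaves room for treatment to change over 12 months.

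If arm shifts medication, adjusting for it does two things. It removes the part of the effect that runs through medication. It also conditions on a variable that may share unmeasured causes with HbA1c, because prescribers respond to poor control; that can produce a difference where none exists. At stake is the main efficacy estimate, in a study whose primary objective includes preliminary efficacy for glycaemic control and which says it is powered to estimate effect sizes.

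**Working it through.** **The plan's own figure.** The plan gives no figure for the medication adjustment. Its only related figure is 80% power at an effect size of 0.65 with N = 90 and a correlation of at least 0.7. The residual SD is sqrt(1 - 0.7^2) = 0.714. With 45 per arm and 0.65 in outcome-SD units, power is about 99%, so 80% is not reproduced. It returns if the correlation is not credited and an unstated 15% attrition is assumed: 38 per arm, and 76/(1 - 0.15) = 89.4, rounded up to 90. The stated power is conservative, and the present point does not depend on it.

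**Inputs.** From the documents: 45 per arm (90 at 1:1), correlation 0.7, two-sided 5% test, ANCOVA on baseline. Assumed: intensification rates, drug effect, and the latent correlation ρ between intensification and unmeasured worsening.

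**Model, in SD units.** Y = 0.7·B + d·A + g·M + 0.714·U. B is baseline, A is arm, M is intensification (yes/no), and U is unmeasured worsening. The total effect is d + g·(p1 - p0), where p1 and p0 are the intensification rates. Adding M to the model moves the arm coefficient to approximately: total - (within-arm slope of Y on M)·(p1 - p0).

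**1. Effect removed.** Set p1 = 45%, p0 = 25%, g = -0.8, d = 0, ρ = 0.
- Total: -0.8 × 0.20 = -0.16.
- Adjusted: -0.16 - (-0.8 × 0.20) = 0.00.

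**2. Effect created under a true null.** Set p1 = 40%, p0 = 25%, g = 0, d = 0.
- Slope: 0.714·ρ·(0.386 + 0.318)/(0.240 + 0.1875) = 1.176·ρ. The numerators are normal densities at the two thresholds; the denominators are p(1 - p).
- Shift: -0.15 × 1.176·ρ = -0.176·ρ.

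| ρ | Adjusted estimate (true 0) | Type I error (simulated) |
|---|---|---|
| 0 | 0.00 | about 5% |
| 0.3 | -0.05 | about 6% |
| 0.5 | -0.09 | about 10% |
| 0.7 | -0.12 | about 16% |
| 0.9 | -0.16 | about 29% |

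Without M, the error stays at about 5% throughout. A repeat simulation agreed to within about 1.5 percentage points.

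**3. Controls intensify more.** Set p1 = 11%, p0 = 25%, g = -0.8, d = -0.42.
- Total: -0.42 + 0.8 × 0.14 = -0.31.
- Adjusted: -0.42. The rejection rate goes from 46% to about 76%.

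**4. At the plan's effect size.** Treat medication as continuous. A shift of 0.8125 SD by arm with -0.4 per SD carries -0.325 of a total of -0.65. The adjusted estimate is -0.33, and the rejection rate falls from 99% to 65%.

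**5. Arm does not affect medication.** With a total of -0.65, the estimate is -0.65 both ways, with power 99% without M and 99.6% with M. There is no bias.

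**The case against.** Several stronger readings are tempting, and the documents do not carry them.

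- **That the primary model is settled as medication-adjusted.** The sentence defining the primary ANCOVA names only baseline HbA1c. The medication sentence comes later, does not use the word primary and gives no model form. This stands as a limit on the charge. It does not remove it, because the later sentence covers the HbA1c analysis without exception.
- **That the adjustment contradicts the intention-to-treat commitment outright.** Sample Size says "intention-to-treat analysis with multiple imputations", which mainly fixes who is analysed, in which arm, and how gaps are filled. A covariate removes nobody and moves nobody between arms. The tension is with the total effect of assignment that this basis implies but the article does not spell out.
- **That adherence coaching proves the covariate lies on the causal path.** Adherence has its own instrument, the Medication Adherence Rating Scale. The adjusted variable is the regimen and dose, which better adherence to an unchanged prescription need not move.
- **That AI4DM routinely sends participants to their physician.** The guidance is conditional: it applies to questions judged to need a detailed medical profile.
- **That the adjusted estimate is neither a total nor a direct effect.** In cases 1 and 3 above it recovers the direct effect (0.00 and -0.42). It fails as a direct effect only when medication change shares unmeasured causes with HbA1c.

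The pilot status lowers the stakes of a single p-value, but not of an effect size meant to inform later work. Nor is this a detail left to an analysis plan: the article positively states the adjustment.

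**Conclusion.** The text is wrong as written. Followed literally, it adjusts the primary outcome for a post-randomisation variable that the intervention's own content could affect, and it does not sit clearly with the sentence defining the primary ANCOVA.

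The harm is conditional. If arm affects medication or dosage, the adjusted estimate is not the total effect of assignment, and it may not be a valid direct effect either. If arm does not affect them, nothing is lost. The documents do not show which will hold; no passage states that AI4DM changes prescriptions, and the route through monitoring and physician contact is plausible rather than documented.

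The bias cannot be signed in advance: the estimate moved towards zero in cases 1 and 4 and away from it in cases 2 and 3. All sizes rest on assumed intensification rates, drug effects and latent correlations. They show possible scale, not a forecast. The 16% type I error in particular needs a latent correlation of about 0.7 and no drug effect on HbA1c.

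**What to change.** 1. In Statistical Methods, restrict the primary HbA1c ANCOVA to pre-randomisation covariates: baseline HbA1c and, optionally, baseline medication and dosage.
2. State that HbA1c is analysed as observed, whatever medication changes follow.
3. Report medication and dosage change by arm as a result in its own right.
4. Move adjustment for 3-, 6- and 12-month medication to a labelled supplementary or mediation analysis, with its assumptions stated, including no unmeasured common causes of medication change and HbA1c.
5. Amend the purpose wording in Table 2 and in the Medication and Dosage section to match.

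The cost is wording only. The plan already provides for collecting these data at all four time points, no participants are added, and the sample-size basis does not change.
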